**Methods:**

The proposed research is a single-site, mixed methods, single-arm cohort study evaluating MBC. Eligible participants will have chronic breathlessness as defined by a modified Medical Research Council score of at least 2 and COPD confirmed by spirometry. Initially, participants will undergo a holistic medical assessment to understand factors contributing to breathlessness and to optimize therapy. The MBC intervention will be a 9-week, home-based, multidisciplinary program (with contributions from medical, nursing, physiotherapy, and occupational therapy clinicians). Central to this program will be coaching for breathlessness self-management using individualized, multicomponent strategies. Breathlessness impact will be assessed using questionnaire instruments measuring breathlessness mastery, symptom burden, quality of life, and psychological distress, with the Chronic Respiratory Questionnaire’s mastery subscale as primary outcome. Assessments will be undertaken at baseline, 9 weeks, and 52 weeks; 12-month exacerbation rates, health care use, and rescue medication use will be monitored and measured against participants’ historical data. Participant and carer experiences will be evaluated using qualitative methods to inform development of the service.

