## Introduction

Chronic obstructive pulmonary disease (COPD) is a multisystem disease, primarily affecting the lungs and characterized by incompletely reversible airflow obstruction [1]. COPD is common, affecting 10% of adults worldwide and 14% of Australians aged >40 years [2]. Despite treatment according to guidelines, people with COPD experience a range of symptoms. Breathlessness is often prominent among these and may contribute to physical and psychological distress, and reduced functional status and community participation [1]. Breathlessness is responsible for a high proportion of ambulance presentations, medical admissions, and health care costs [3,4]. However, patients with refractory breathlessness and their caregivers feel that there is a lack of awareness of the symptom burden among health care providers and insufficient provision to address this burden within health care services [2,5,6].

Breathlessness intervention services have been clearly shown effective in reducing the burden of breathlessness for populations with malignant and mixed etiology disease [7]. Existing breathlessness intervention service research primarily targets participants with malignant disease, in Europe, over a 4- to 6-week period, led by clinicians whose expertise is in palliative care [7]. An Australian protocol for a single-blind, randomized, parallel-group study investigating the impact of a breathlessness intervention service on people with COPD has been published; however, the study outcomes are not yet fully reported [8].

The primary aim of this study is to assess whether participants living with COPD will experience reduced breathlessness impact following participation in a bespoke 9-week intervention, the Macarthur Breathless Clinic (MBC), focused on nonpharmacological interventions such as breathing retraining, energy conservation, physical activity, and use of a handheld electric fan. A secondary aim is to monitor participants’ exacerbations, health care use, and rescue medication use after the intervention for comparison with past patterns of disease activity. Furthermore, we will use qualitative methods to assess patient and caregiver experiences.

The hypothesis is that patients with COPD will experience (1) reduced impact of breathlessness (in terms of coping ability, symptom burden, quality of life, and psychological distress); (2) reduced COPD-related health care use; and (3) report a positive consumer experience following participation in the MBC.

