### Outcome Measures

#### Breathlessness Outcomes

The proposed primary outcome is mastery of breathlessness, as measured by the Chronic Respiratory Questionnaire (CRQ) subscale of mastery [12].

The proposed secondary outcomes, described below, will measure the impact of the intervention using several scales to provide a full understanding of change across a number of dimensions.

The CRQ is a validated measure of quality of life used in chronic lung diseases, with a particular emphasis on breathlessness. It consists of 4 subscales: dyspnoea, fatigue, emotion, and mastery. In each scale, higher scores reflect better health. The minimal clinically important difference (MCID) for each subscale individually is an increase of 0.5 on a 7-point scale, with a change of 1 representing a moderate change and 1.5 a large change [12].

For breathlessness intensity, unpleasantness, and confidence numerical rating scales, international guidelines recommend assessing both intensity and unpleasantness of breathlessness [13]. The MCID for these measures is a change of 1 unit [14].

The COPD Assessment Test (CAT) is a validated 8 item tool that provides a reliable measure of the impact of COPD on a patient’s health status. Higher scores reflect worse health with an MCID of 2 [15].

The Hospital Anxiety Depression Scale is a 14 item self-reported measure with anxiety and depression subscales each with 7 items. An MCID of 1.5 points for Hospital Anxiety Depression Scale in COPD populations has been suggested [16].

The EQ-5D-5L is a standardized measure of health status that provides a simple, generic measure of health for clinical and economic appraisal. The scale explores the degree of difficulty across 5 domains: mobility, self-care, usual activities, pain or discomfort, and anxiety or depression. A weighted index value will be derived, ranging between −0.59 and 1, which can be converted to quality-adjusted life years based on the Australian values set. Higher scores reflect better health, and the mean MCID is 0.051. It also includes a visual analog scale 0 to 100, rating overall health from worst to best with a mean minimum important difference of 6.9 (range 6.5-8.0) [17].

Pedometer readings of average number of steps per day over the past 7 days will be recorded. There is no consensus regarding the MCID for this measure.

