#### Statistical Analysis Plan

Descriptive statistics will be applied to the study population to characterize them in terms of demographic and baseline clinical parameters. Normally distributed continuous variables will be expressed as mean (SD), nonparametric variables will be defined by median and range, while categorical variables will be expressed as percentages.

Breathlessness outcomes will be compared across 3 time points: baseline, 9 weeks, and 52 weeks using repeated measures ANOVA. Predictors of response will be sought using linear regression models with sex, forced expiratory volume (FEV) in 1 second, ratio of FEV to forced vital capacity, BMI, Montreal Cognitive Assessment, and baseline anxiety and depression scores as prespecified variables. Health care use measures and exacerbation data for the 12 months prior to MBC enrollment will be compared with the corresponding values for the 12 months after MBC enrollment, using Student 2-tailed *t* tests or nonparametric tests as appropriate. Protocol completer and dropout populations will be compared in terms of baseline characteristics (sex, age, FEV in 1 second, pack years, BMI, CRQ-Mastery subscale, CAT score, and Montreal Cognitive Assessment) to investigate potential selection bias.

Finally, comparison will be made with patients’ baseline data from the year prior to enrollment in the breathless clinic, benchmarked against nonparticipant comparator hospital deidentified patient medical records with (1) ED presentations for reasons of breathlessness, triaged as “shortness of breath—respiratory” or (2) hospitalized with exacerbations of COPD or heart failure as per diagnostic related group assignment. These benchmarking comparisons will use deidentified electronic medical records and will contribute to exploratory analyses undertaken to better understand the health care use of our sample cohort in the context of the overall health care use patterns of our local population “breathless” groups.

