### Strengths and Limitations

The study’s focus on a homogeneous disease population of patients with moderate to severe COPD will ensure that the results are highly relevant to this specific group. This targeted approach will allow for more precise conclusions regarding the usefulness in this cohort of the intervention being tested. That said, we will recruit a wide range of patients with COPD in terms of severity and exacerbation susceptibility, ensuring broad applicability to this important, and large, patient group. Thus, our results will complement the existing evidence base, as most previously published data include more heterogeneous participant populations; patients with malignant disease, and/or patients with a variety of restrictive and obstructive nonmalignant respiratory disease.

To our knowledge this is the first long-term study protocol for this type of intervention service. By spanning a longer period, an entire year, the study will mitigate the potential confounding effects of seasonal variations in COPD symptoms and exacerbations. This will ensure that the observed outcomes are more likely attributable to the intervention rather than external seasonal factors. Additionally, the proposed intervention requires behavior change, which can take time to implement. By having a longer duration than previous interventions, we hope to enable patients to embed into their routine the suggested nonpharmacological strategies and to thus realize a durable effect beyond the 9 weeks of the program.

The 12-month follow-up period will also provide insight into the durability of the intervention response over a prolonged period. To date, the scientific literature contains few reports of outcomes for this type of intervention extending beyond 2 or 3 months. Showing sustained symptomatic benefits for this type of population with nonmalignant, chronic disease is perhaps much more important than demonstrating a short-term response.

Finally, the use of the CAT as a key assessment tool will underscore the study’s relevance to clinical practice. The CAT is a validated, disease-specific instrument that provides a comprehensive evaluation of COPD symptoms and their impact on patients’ quality of life. This may allow for the MBC to be ranked against other treatment interventions used in COPD, so that any positive study findings can be integrated into existing treatment paradigms, thereby facilitating the translation of research into practice.

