However, this study has several limitations that must be acknowledged. First and foremost is the nonrandomized study design; all recruited participants will receive the intervention and act as their own controls. This design could introduce both time and attrition bias and is a clear limitation on the level of evidence produced. The authors were aware of a randomized controlled trial [8] underway in another Australian center using a similar model to our protocol, and we therefore chose a nonrandomized study design to address clinical need while still demonstrating translatability to a different population and setting. Given that COPD is a chronic and progressive disease, evaluating the impact of breathlessness over time may still yield valuable insights, provided the results are interpreted carefully. While potential mortality among participants with more severe disease may skew study results, on the other hand, worsening disease trajectory may mask benefits when determining results over the longer term. Considering this, even if patients appear to be stable with respect to outcome measures at 12 months, this may actually represent improvement compared with the expected trajectory in COPD, which is one of deterioration. In fact, clinically significant breathlessness is a known marker of poor prognosis for patients with COPD [21], and so our target population will be expected to deteriorate more rapidly than the COPD group as a whole.

The study’s proposed setting, a single metropolitan center situated within a large semirural area, may limit the general applicability of our results. However, the authors are aware of concurrent research on this topic being conducted at other centers and health districts throughout Australia, which should help to address this.

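### No primary time point or contrast is stated for CRQ mastery, and the omnibus three-time-point ANOVA does not test the directional hypothesis

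*Protocol article*

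**What the plan says.** Under Breathlessness Outcomes the Protocol article states: "The proposed primary outcome is mastery of breathlessness, as measured by the Chronic Respiratory Questionnaire (CRQ) subscale of mastery". No time is given there. The abstract (Methods) lists the visits: "Assessments will be undertaken at baseline, 9 weeks, and 52 weeks". The Introduction gives the aim, again without a visit: "The primary aim of this study is to assess whether participants living with COPD will experience reduced breathlessness impact following participation". The hypothesis has a direction, "reduced impact of breathlessness (in terms of coping ability, symptom burden, quality of life, and psychological distress"), and Breathlessness Outcomes defines the MCID as a rise of 0.5 on a 7-point scale on which higher is better.

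The Statistical Analysis Plan section then says: "Breathlessness outcomes will be compared across 3 time points: baseline, 9 weeks, and 52 weeks using repeated measures ANOVA". It names no contrast, direction or success rule for the primary outcome.

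Two remarks under Strengths and Limitations bear on how the result would be read. On the later visit: "Showing sustained symptomatic benefits for this type of population with nonmalignant, chronic disease is perhaps much more important than demonstrating a short-term response". On no change at that visit: "even if patients appear to be stable with respect to outcome measures at 12 months, this may actually represent improvement", the comparison being with an expected course of deterioration. The same paragraph says that a worsening disease course may hide benefit in the longer term. It also asks for careful interpretation.

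**The concern.** The assessment time is part of the definition of a primary outcome. Here two follow-up visits are candidates, and the one stated test covers both at once without regard to direction. A significant F would not by itself show that mastery improved. A reader would have to look at the means and then decide which visit counts.

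That decision is open while, according to the Results section, data collection is finished and analysis is under way. The Discussion adds two readings of week 52: stability may be improvement, and decline may be masked benefit. Neither is tied to a comparator or to a stated expected change in CRQ mastery. The benchmarking against hospital records in the Statistical Analysis Plan concerns health care use, not mastery. What is at stake is how much a positive claim on the primary outcome would tell the reader.

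**Working it through.** **Inputs from the Protocol article.** Three time points and the ANOVA (Statistical Analysis Plan); MCID 0.5 (Breathlessness Outcomes); 92 recruited with 30% (n=31) dropout expected (Sample Size). The last gives 92 − 31 = 61 or 92 × 0.70 ≈ 64 completers. The Results section speaks of 92 finishing, so 92 is also shown.

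**Assumptions.** The article gives no SD, within-person correlation or alpha for this analysis. I take SD 1.0 to 1.5, correlation ρ 0.5 to 0.7, two-sided alpha 0.05 and compound symmetry. There is no power calculation in the article to reproduce.

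**Step 1: the F test is blind to direction.** Its noncentrality is λ = n × Σ(μⱼ − μ̄)² / [SD² × (1 − ρ)], with 2 and 2(n − 1) degrees of freedom. For mean changes (baseline, week 9, week 52) of (0, 0, −0.5), μ̄ = −1/6 and Σ(μⱼ − μ̄)² = 1/36 + 1/36 + 1/9 = 1/6. With n = 64, SD 1.2 and ρ 0.5:

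λ = 64 × (1/6) / (1.44 × 0.5) = 10.67 / 0.72 = 14.8

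| Mean changes at weeks 0, 9, 52 | Σ(μⱼ − μ̄)² | λ | Chance that F is significant |
|---|---|---|---|
| 0, +0.5, +0.5 (sustained gain) | 1/6 | 14.8 | 94% |
| 0, +0.5, 0 (gain lost by week 52) | 1/6 | 14.8 | 94% |
| 0, 0, −0.5 (no gain, later loss) | 1/6 | 14.8 | 94% |
| 0, −0.25, −0.5 (steady loss) | 1/8 | 11.1 | 85% |
| 0, 0, 0 (no change) | 0 | 0 | 5% |

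The first three rows have the same λ: the test treats a sustained gain and a later loss alike.

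**Step 2: range for no week-9 gain and a 0.5-point week-52 loss** (noncentral F).

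| SD, ρ | n = 61 | n = 64 | n = 92 |
|---|---|---|---|
| 1.0, 0.5 | 98% | 99% | >99% |
| 1.0, 0.7 | >99% | >99% | >99% |
| 1.2, 0.5 | 92% | 94% | 99% |
| 1.2, 0.7 | 99% | >99% | >99% |
| 1.5, 0.5 | 76% | 78% | 92% |
| 1.5, 0.7 | 94% | 95% | 99% |

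Simulation at n = 61 gives 74% to 100% over the same range. In 71% to 97% of those trials F is significant while neither visit shows a significant improvement.

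**Step 3: an open choice of visit.** With one named contrast at two-sided 0.05, the chance of a false finding of improvement is 2.5%. If either visit may be chosen without first requiring a significant F, simulation gives about 4% to 5% for improvement and 8.4% to 9.7% for a difference in either direction (independence bound 1 − 0.95² = 9.75%).

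**Step 4: what stability means at week 52.** With n = 64 and an SD of change of 1.2 (SD 1.2 at ρ 0.5), the 95% CI half-width is 1.998 × 1.2 / √64 = 0.30. For an SD of change of 1.0 to 1.5 it is 0.25 to 0.38, at least half the MCID. With no true change, week 52 does not differ significantly from baseline in about 95% of trials, so the stability reading would nearly always be available.

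**The case against.** The strongest reply is that the visit order can be inferred. Study Design evaluates outcomes before and after the clinic and assigns durability to the 12-month follow-up, and Anticipated Findings speaks of change from baseline after a 9-week programme. Follow-up contrasts after an ANOVA are often left to a full plan, and a registered time point may exist. This stands in part: week 9 for effect and week 52 for durability is the natural reading. But the article never states it, it has a section headed Statistical Analysis Plan that states the test, and it ranks sustained benefit above the short-term response.

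A reader might infer that deterioration could be presented as support, or that the study cannot fail. The documents do not say this. The hypothesis and the MCID have a direction, decline is said only to hide benefit, and a significant F driven by falling means would be visible and would contradict the hypothesis.

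A reader might also treat the stability remark as a decision rule. It is a hedged sentence in the limitations, accompanied by a call for caution and an admission that the design limits the evidence. Nor do the documents show that the sickest participants were lost: mortality is mentioned as a possibility, and the Results section reports 92 finishing. Finally, the F test keeps its 5% level under no change, so the fault is one of relevance, not of inflated error.

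**Conclusion.** The point holds in this form: no primary time point or contrast is stated for CRQ mastery, and the only stated test does not answer the directional hypothesis. With 61 to 64 completers the test would be significant in roughly 74% to 100% of trials with no week-9 gain and a 0.5-point week-52 loss, and in more than 90% with 92. These figures rest on the assumed SD and correlation and on a loss as large as the MCID. The blindness to direction does not depend on them.

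The secondary point also holds. Without a control group or a stated expected decline in CRQ mastery, a 52-week result that is flat or worse does not clearly count against the hypothesis, because the Discussion supplies a favourable or excusing reading for each. How open the visit choice really is remains uncertain, since the registry entry and any fuller plan were not available.

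**What to change.** - Make one change-from-baseline contrast in CRQ mastery primary: the registered time point if one exists, otherwise baseline to week 9. Report the estimate with its 95% CI and read it against the 0.5 MCID.
- Make baseline to week 52 a secondary durability contrast, reported in the same way. The ANOVA can stay as a supporting description.
- State when this choice was made relative to seeing outcome data. With collection finished and analysis under way, it cannot be presented as prespecified unless a dated record shows that.
- State that a 52-week CI including 0 is inconclusive without a comparator. Remove the reading of stability as improvement, or tie it to an external estimate of decline in CRQ mastery fixed beforehand.

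The cost is wording in the analysis plan and Discussion before results are reported; no new data are needed. A single named contrast at n = 61 has a power of about 72% to over 99% for a 0.5-point change under the same assumptions. The downside is that an unchanged 52-week score can no longer be presented as benefit.

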## Methods

### Study Design

This research is a prospective, single-arm cohort study of MBC, a breathlessness intervention service, assessed using mixed methods. The intervention is designed to adapt to incorporate components found to work well and to discard or revise those found to be less effective, informed by the experience of conducting the program.

Quantitative outcomes will be evaluated with participants acting as their own controls, before and after the clinic intervention. A 12-month follow-up with sequential cross-sectional assessments will provide an opportunity to assess breathlessness impact, exacerbations, health care use, and durability of outcomes. Qualitative outcomes for patients and their carers, if applicable, will be sought via an interviewer-administered survey in the months following completion of the clinic intervention. A flow diagram overview of the study design is shown in Figure 1.

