## Discussion

### Anticipated Findings

This study adds to the literature by evaluating the change from baseline after a 9-week multidisciplinary, home-based health intervention to address the symptom of breathlessness in a cohort of Australian patients who have moderate to severe COPD. The study based on this protocol will provide important insights into applying this type of intervention to patients with COPD, a chronic disease. The authors anticipate that this study will help to inform models of care for patients with COPD enduring breathlessness as a persistent and distressing symptom, providing information about the potential durability of these interventions, and the characteristics of patients with COPD who might be most likely to benefit.

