### Comparison With Prior Work

Breathlessness intervention services have been shown to be effective for breathlessness over the short term [7] The first examples of these services targeted patients with malignant disease, using complex, multicomponent, nonpharmacological interventions for the management of breathlessness [20]. Subsequent trials enrolled heterogeneous populations of patients with a mixture of malignant and nonmalignant diseases, including some patients with COPD. The authors are aware of a recently completed randomized controlled trial in Australia targeting a population of patients with COPD using a breathlessness intervention model similar to our own. Breathlessness in COPD often remains persistent and distressing despite best pharmacological treatments. However, COPD is a chronic disease, and so patients may live for many years with this burden. For these patients, not only are effective treatment strategies needed but benefit must be sustained over the long term. The proposed protocol uses a multidisciplinary home-based complex health service intervention similar in type to those known to confer significant short-term benefits for breathless patients in mixed disease populations, aiming to confirm its applicability to breathless patients with COPD, and also exploring the durability of benefits and best selection of patients.

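### In a single arm, the regression for predictors of response finds correlates of change from baseline and cannot show who benefits from the clinic or who should be selected for it

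*Protocol article*

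**What the plan says.** Study Design fixes a single arm: "This research is a prospective, single-arm cohort study of MBC, a breathlessness intervention service, assessed using mixed methods". The comparison is within patients: "Quantitative outcomes will be evaluated with participants acting as their own controls, before and after the clinic intervention".

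The Statistical Analysis Plan section states: "Predictors of response will be sought using linear regression models with sex, forced expiratory volume (FEV) in 1 second", then the FEV1/FVC ratio, and "BMI, Montreal Cognitive Assessment, and baseline anxiety and depression scores as prespecified variables". That makes seven variables if anxiety and depression are counted separately. The section does not call this regression exploratory, although it uses that word for the benchmarking against hospital records.

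The Discussion gives the reading intended for such results. Anticipated Findings expects information on "the characteristics of patients with COPD who might be most likely to benefit". Comparison With Prior Work describes the study as "also exploring the durability of benefits and best selection of patients".

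Strengths and Limitations concedes time and attrition bias for the design in general and says the expected course in COPD is deterioration. It does not apply either remark to the predictor analysis.

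**The concern.** Who benefits most is a question about effect modification: does the clinic's effect differ by FEV1, sex, BMI and so on? The regression tests something else, namely whether observed change is related to the variable. In one arm, observed change is the clinic effect plus whatever would have happened anyway. A variable that only marks the patient's own course can therefore be reported as marking response.

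At stake is the patient-selection conclusion. If a severity marker were read as a responder marker when it only reflects slower decline, the published result could suggest favouring some patients over others who gain just as much. A fuller analysis plan could not repair this. Whatever dependent variable it named (change or follow-up score, 9 or 52 weeks), there would still be no untreated comparison.

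**Working it through.** **1. What the slope estimates.** This step needs no assumed figure. For patient i,

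change_i = N_i + B_i + (e1_i − e0_i),

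where N is untreated change, B is benefit from the clinic, and e0 and e1 are the transient parts of the baseline and follow-up scores. Regressing change on a baseline variable X gives

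slope(X) = slope of N on X + slope of B on X − slope of e0 on X.

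Only the second term concerns differential benefit; the third is regression to the mean. In a two-arm study the treatment-by-X interaction isolates the second term. In one arm that contrast does not exist. Adding baseline mastery as a covariate would remove part of the third term and leave the first untouched.

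**2. Whether another part of the plan supplies the missing comparison.** The nonparticipant benchmarking in the Statistical Analysis Plan section concerns health care use, so it gives no untreated course for the breathlessness scores.

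**3. Inputs for an illustration.**
- n: Sample Size gives 92 recruited and 31 expected losses, so 92 − 31 = 61. (31/92 is 33.7%, not the stated 30%; this point does not depend on it.) Results says 92 finished the protocol, so both 61 and 92 are shown.
- Benefit: +0.5 for every patient, the minimal clinically important difference given under Breathlessness Outcomes. Because it is constant, the true difference in benefit is zero.
- Assumed, not in the documents: SD of change about 1.0 apart from the FEV1 effect; correlation of 0.6 between FEV1 and the FEV1/FVC ratio, and of 0.6 between anxiety and depression; prognostic slope b of FEV1 on untreated change of 0 to 0.4 per SD. The model holds the seven listed variables, each tested two-sided at 0.05.

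**4. Closed-form check.** With seven predictors, the noncentrality of the FEV1 t test is about b × √[(1 − 0.6²)(n − 7)] / 1.0.
- n=61: √(0.64 × 54) = 5.88. For b = 0.2, 0.3 and 0.4 this gives 1.18, 1.76 and 2.35. With 53 degrees of freedom (critical value 2.006) the rejection rates are about 21%, 41% and 64%.
- n=92: √(0.64 × 85) = 7.38, giving 1.48, 2.21 and 2.95. With 84 degrees of freedom (critical value 1.989) the rates are about 31%, 59% and 83%.

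**5. Simulation, 1,500 trials per scenario.** The ranges run over 0%, 20% and 40% of baseline-anxiety variance shared with the transient part of baseline mastery.

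| FEV1 slope per SD | FEV1 named, n=61 | FEV1 named, n=92 |
|---|---|---|
| 0 | about 5% | about 5% |
| 0.2 | 20–25% | 31–36% |
| 0.3 | 42–46% | 57–63% |
| 0.4 | 64–69% | 80–89% |

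In a simulated two-arm design (total n 92 or 184) with the same slopes, the interaction test rejected in 4.5% to 6.1% of 3,000 trials.

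**6. Regression to the mean alone.** In the same simulation, without baseline mastery in the model, baseline anxiety was named in about 36–40% of trials at n=61 when 20% of its variance was shared with transient baseline mastery, and in 64–66% when 40% was shared.

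**7. Sensitivity.** In a variant with baseline mastery added and FEV1 correlated 0.3 with untreated change (n=61), the rate is about 60% with independent predictors. It is about 49% with a correlation of 0.5 within the FEV1–ratio and anxiety–depression pairs, and about 37% with 0.7. If only 70% of the variance of change is true change, the last two fall to about 37% and 26%.

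**The case against.** Patient selection is not a declared objective. Neither the abstract's Objective nor the aims and hypotheses in the Introduction mention it. The Discussion wording is hedged (might be, exploring), and Future Directions lists patient selection as still open. This stands, and it limits the point to one secondary analysis and its interpretation. The hedges soften the certainty of the claim, though, and leave its target as benefit.

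The limitation is also partly disclosed. Strengths and Limitations puts the nonrandomized design first and asks for careful interpretation. That stands for the before-and-after comparison, but the caveat is never carried to the regression.

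A reader might infer that the protocol itself says course varies with FEV1 inside this cohort, from "our target population will be expected to deteriorate more rapidly than the COPD group as a whole". It does not. That sentence compares the whole target population with COPD patients generally, and breathlessness grade is not among the listed predictors. The nearby remark on mortality in more severe disease concerns who is lost, not untreated change in mastery. That FEV1 predicts untreated change is therefore an assumption.

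A reader might also infer that the 9-week regression is safer than the 52-week one because decline has had less time to act. The documents do not support that ranking. Recruitment allows entry after stabilization following an admission, and only exacerbations within 4 weeks are excluded, so early recovery or regression to the mean could affect the 9-week change.

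**Conclusion.** The point holds on the design and the text alone: a one-arm regression identifies correlates of change, and the step from there to who benefits or who should be selected is unsupported whatever the p-value.

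The size is conditional. If no listed variable is related to untreated change or to transient baseline variation, each test keeps its 5% error. If FEV1 has a prognostic slope of 0.2 to 0.4 per SD, it is named in roughly 20–69% of trials at n=61 despite identical benefit. Those rates already include a 0.6 correlation between FEV1 and the ratio; stronger correlation or noisier outcomes would lower them, and weaker correlation would raise them. They illustrate direction and do not estimate what will happen in this study. Nothing in the documents shows that a false selection marker will be found, or that access to the service will be decided on one.

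**What to change.** In the Statistical Analysis Plan section, call the analysis *exploratory predictors of change from baseline (prognostic associations)* and add that a single arm cannot separate these from effect modification. In Anticipated Findings and Comparison With Prior Work, replace the wording on benefit and selection with *characteristics associated with change after the program, as hypotheses for controlled studies*. Do not rank the 9-week regression above the 52-week one on the ground of disease course.

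No new data or analysis is needed, and with analysis still under way the change can be made before results are reported. The cost is a weaker claim about patient selection.
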